### Contraindications:

The Investigator and study staff must be thoroughly aware of all contraindications and other information contained in the Package Insert for SP (Fansidar), AZ (Zithromax), CQ (Arelen), and IB for the study medication AZCQ.

### 5.1. Allocation to Treatment

The investigator's knowledge of the treatment must not influence the decision to enroll a particular subject or affect the order in which subjects are enrolled. Refer to Section 4.3 (Randomization Criteria) for details.

090177e1811dafca\Approved\Approved On: 22-Feb-2010 14:41

## 5.2. Breaking the Blind

The study is open label. However, the microbiologists (microscopists) will be blinded to the study treatments of the subject and the reading of other microscopists. The lab scientists undertaking the laboratory investigations (ie, molecular assays, biochemical assays, histological and microbiological investigations) will be unaware of the study group from which the sample was obtained.

## 5.3. Drug Supplies

All trial medication will be supplied by Pfizer.

AZ and CQ will be administered as a combination tablet containing 250 mg AZ and 155 mg CQ base. This is a research tablet, and is not approved for commercial use.

Commercial SP (Fansidar®) from Roche will be used in this study. Each tablet contains 500 mg sulfadoxine/25 mg pyrimethamine.

### 5.3.1. Formulation and Packaging

AZ and CQ fixed-dose combination tablets AZCQ will be supplied in unit dose bottles. Fansidar® will be supplied by Pfizer with an ancillary label applied to the commercial container.

Pfizer will perform the labeling and distribution of the clinical supplies in accordance with applicable regulatory requirements.

### 5.3.2. Preparation and Dispensing

Only qualified personnel who are familiar with procedures that minimize undue exposure to them and to the environment should undertake the preparation, handling, and safe disposal of chemotherapeutic agents.

AZCQ will be dispensed to a subject for oral administration once daily for three days of therapy. Similarly, SP will be dispensed from the commercial package and administered orally for once daily.

### 5.3.3. Administration

All study drugs will be administered as open label therapy under supervision. Study medication will be dispensed by the Investigator or designee (Section 5.3.2). AZCQ and SP should not be administered on an empty stomach. Each dose should be administered with a glass of water.

- AZCQ treatment: first dose of each AZCQ treatment course will be administered under supervision during the ANC visit. Subsequent two doses will be administered at home by fieldworker(s).

- SP treatment: each dose of SP treatment course will be administered under supervision during the ANC visit.

Each subject will receive three IPTp treatment courses of AZCQ or SP during ANC visits at 4 - 8 week intervals. The first treatment course will be administered during the second trimester (14-26 weeks of gestation as confirmed by ultrasound). The last treatment course should be given to subjects prior to or during 36 weeks of gestation.

Any dose that is vomited within 30 minutes of administration will be repeated. If vomiting re-occurs after the re-dose, the subject will not receive further study treatments but will be referred to the investigator and will be given standard ANC care. If subjects in AZCQ group vomit after re-dose during first or second treatment course, they will be given additional course(s) of standard IPTp courses with SP. If vomiting on re-dosing of AZCQ happens during the home visits, subject will be advised to return to the study site within 7 days for appropriate treatment by the study physician. All subjects will be followed through Visit 6 on Day 28 (window Day 28 - Day 42) post delivery.

#### **5.3.4. Compliance**

The medication will be administered to the subject under supervision by investigators or site study team members during ANC visit or at home by the fieldworkers.

#### **5.4. Drug Storage and Drug Accountability**

The investigator, or an approved representative (eg, pharmacist), will ensure that all study drug is stored in a secured area, under recommended storage conditions and in accordance with applicable regulatory requirements. Prior to dispensing, all study medications should be stored under the conditions per label instructions. The investigator will be responsible for recording the receipt and usage of all drugs supplied and for ensuring the supervision (via the hospital pharmacist or fieldworker where relevant) of the storage and allocation of these supplies. To ensure adequate records, all study drugs will be accounted for in the case report form and drug accountability inventory forms as instructed by Pfizer.

The investigator or designee must maintain adequate records documenting the receipt, use, loss, or other disposition of the investigational products. Pfizer may supply drug accountability forms that must be used or may approve use of standard institution forms. In either case, the forms must identify the investigational products, including batch or code numbers, and account for its disposition on a subject-by-subject basis, including specific dates and quantities. The forms must be signed by the individual who dispensed the drug, and copies must be provided to Pfizer.

At the end of the trial, Pfizer will provide instructions as to disposition of any unused investigational products. If Pfizer authorizes destruction at the trial site, the investigator must ensure that the materials are destroyed in compliance with applicable environmental regulations, institutional policy, and any special instructions provided by Pfizer. Destruction must be adequately documented.

### 5.5. Concomitant Medication(s)

Medications consistent with the Package Inserts of AZ and CQ are allowed in the AZCQ group. However, to avoid interfering with the evaluation of the study drugs, subjects in the AZCQ group must not take SP during the course of the study unless they need to be switched to SP IPTp regimen consequent to their withdrawal from the AZCQ IPTp regimen because of any safety or tolerability issues related to AZCQ use. Subjects in the SP group must not take AZ and/or CQ during the participation of the study but other medications consistent with the Package Inserts of Fansidar are allowed. The medications that are contra-indicated during pregnancy should be avoided. All medications used by the subject at study entry or at any time during participation in the study must be recorded in the case report form. At each study visit, all medications taken since the last evaluation will be recorded.

While interactions with digoxin, ergot alkaloids, triazolam, carbamazepine, cyclosporine, hexobarbital and phenytoin have not been reported in clinical trials with AZ, they have been observed with macrolide products. Careful monitoring of subjects taking these medications is advised.

A single oral dose of AZ co-administered with nelfinavir at steady-state resulted in increased AZ serum concentrations. Although it is not necessary to adjust the dose of AZ when administered in combination with nelfinavir, close monitoring for known side effects of AZ (eg, liver enzyme abnormalities, hearing impairment) is warranted.

There have been reports which may indicate an increase in incidence and severity of adverse reactions when CQ is used with Fansidar as compared to the use of Fansidar alone (refer to Fansidar package insert). Fansidar is compatible with quinine and with antibiotics.

However, antifolic drugs such as sulfonamides, trimethoprim, or trimethoprim-sulfamethoxazole combinations should not be used while the patient is receiving Fansidar for antimalarial prophylaxis. Fansidar has not been reported to interfere with antidiabetic agents.

If signs of folic acid deficiency develop, Fansidar should be discontinued. When recovery of depressed platelets or white blood cell counts in subjects with drug-induced folic acid deficiency is too slow, folinic acid (leucovorin) may be administered in doses of 5-15 mg intramuscularly daily for 3 days or longer.

Please refer to package inserts for SP, AZ, CQ and IB for AZCQ for further information regarding potential interactions between study drugs and other treatment agents.

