### 1.3.2.3. Clinical Effects of Azithromycin against Sexually Transmitted Infections

Sexually transmitted infections (STI) adversely affect pregnancy and contribute to pre-term delivery, LBW, intrauterine growth-retardation, spontaneous abortion, stillbirth, newborn morbidity and mortality. The prevalence estimates of symptomatic STIs at antenatal clinics in sub-Saharan Africa range between 2.5 and 17% for *T. pallidum*, 1.7 and 7% for *Neisseria gonorrhoeae*, 5.3 to 20.8% for *C. trachomatis* and 7.3% to 62% for chancroid. In addition, a shortcoming to STIs is the asymptomatic infection, which remains undiagnosed and untreated. If untreated in pregnancy, one-third of women will develop congenital syphilis, carrying major risk for the fetus.

AZ has significant activity against selected STIs (eg, *Chlamydia trachomatis*, *Neisseria gonorrhoeae*, *Treponema pallidum*). In a randomized clinical trial involving 4,033 pregnancies in Uganda, the presumptive treatment of STIs in pregnancy improved maternal health and birth outcomes. Vaginal infections were significantly lower in women who received a one-time dose of azithromycin (1,000 mg), metronidazole (2,000 mg) and cefixime (400 mg) compared to women who received iron/folate and low-dose multivitamins. In the treatment group, the relative risk (RR) of *T. vaginalis* was 0.28 (95% CI, 0.18–0.49), the RR of bacterial vaginosis was 0.78 (95% CI, 0.69–0.87), and the RR of infant ophthalmia was 0.37 (95% CI, 0.20–0.70).

Single oral doses of 1000 mg and 2000 mg of azithromycin are recommended for chlamydial and gonococcal infections. In two separate studies conducted in Tanzania, and in United States & Madagascar, a single 2000 mg dose of azithromycin was comparable to the standard dosing regimen of benzathine penicillin in the treatment of early syphilis. Hence, activity of AZ against these infections should provide additional benefit when AZ and CQ combination is used for IPTp in pregnant women.

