#### 1.6.1.2. Azithromycin-Chloroquine (AZCQ)

AZCQ will be administered as three IPTp treatment course regimens during second and third trimester. The first treatment course will be administered at the first ANC visit in second trimester. The subsequent two courses will be administered at 4-8 weeks interval between courses in second/third trimester. Each treatment course will consist of 3-day of dosing: 1000 mg AZ/620 mg CQ, ie, 4 fixed dose tablets of AZCQ (250mg/150mg strength) administered once daily for 3 days. First dose will be administered under supervision at the ANC; subsequent two doses will be administered at home under supervision of a field worker.

**Rationale for AZCQ Dosing Regimen:** The dosing regimen of AZCQ has been selected for the IPTp program for the following reasons:

1. The above 3-day dosing regimen (1000 mg AZ/620 mg CQ, ie, 4 fixed dose tablets of AZCQ (250 mg/150 mg strength) administered once daily for 3 days) was evaluated and demonstrated efficacy in two adult treatment clinical trials (A0661134 and A0661155) in sub-Saharan Africa. Both PCR corrected and uncorrected parasitological efficacy rates were above 90%. For details on studies A0661134 and A0661155 (Refer to Section 1.5.2.2. and the IB).
2. In a clinical pharmacology study in healthy subjects (A0661186), the pharmacokinetics of the fixed dose AZCQ combination tablet appeared to be comparable to that of the individual tablets of AZ and CQ used in earlier adult treatment trials (Refer to Section 1.5.2.1. and the IB).
3. Although pregnant women experience unique physiological changes that can alter drug disposition during gestation, available data and PK modeling suggests that AZ and CQ PK are not significantly different between pregnant and non-pregnant women.
4. A total AZ dose of 3000 mg to be used for each IPTp treatment course is higher than the 2000 mg dose needed for treatment of STIs including *T. Pallidum*, *C. trachomatis*, and *N. gonorrhoea*.

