### **5.7. Treatment for Sexually Transmitted Infection**

Subjects diagnosed with *T. pallidum* at the baseline Day 0 of Visit 1 or any time during the study period will receive standard dosing regimen of benzathine penicillin G consistent with local ANC guidelines.

Subjects presenting with clinical symptoms of *N. gonorrhoeae*, *C. trachomatis*, *T. vaginalis* at any time during the study period will receive appropriate therapies according to local ANC guidelines for treatment of these diseases in pregnancy.

Please refer to Section 5.5 (Concomitant Medications) and/or drug inserts for further information regarding potential interactions between study drugs and other treatment agents.

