## 9.2. Efficacy Analysis

The primary efficacy analysis population (ie, Primary Analysis Set) will be intent-to-treat (ITT) for all endpoints. It will consist of subjects who are randomized, have received at least one dose of study medication (Day 0 at Visit 1 is considered the first dose of study medication), and have a single fetus. Subjects without the required data needed to compute an endpoint will be treated as missing. Analyses will also be performed for as per protocol analysis set, considered secondary. A per protocol analysis set will consist of all ITT subjects who have been compliant with study medication and will exclude subjects who have a neonate birth-weight measured greater than 7 days after birth if they do not already meet the definition of sub-optimal pregnancy outcome, and also exclude subjects who withdraw from study drug and switch to standard of care IPTp treatment. Compliance with study medication will consist of at least 6 of the 9 AZCQ daily doses, and at least 2 of the 3 SP daily doses. Once again, subjects without the required data needed to compute an endpoint will be treated as missing. Sensitivity analyses will be defined for both the ITT and PP populations.

Treatment group comparisons for the primary endpoint will use an overall alpha level of 0.00125 2-sided (equivalent to 0.000625 1-sided), subject to the alpha spending function specified in Section 9.5. Treatment group comparisons for the secondary endpoints will use an overall alpha level of 0.05 2-sided (equivalent to 0.025 1-sided), also subject to the same alpha spending function.

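### Sections 5.5 and 5.7 give an SP-arm woman with symptomatic chlamydia or gonorrhoea two conflicting instructions wherever the local guideline uses azithromycin, and neither section says which prevails

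*Protocol*

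**What the plan says.** - **Section 5.5 (Concomitant Medications):** "Subjects in the SP group must not take AZ and/or CQ during the participation of the study". No exception follows. The sentence before it, which bars SP in the AZCQ arm, does contain an explicit exception for women withdrawn from AZCQ. The same section also makes recording compulsory, on the case report form: "All medications used by the subject at study entry or at any time during participation in the study must be recorded".
- **Section 5.7 (STI treatment):** women in either arm with symptoms of *N. gonorrhoeae*, *C. trachomatis* or *T. vaginalis* at any time in the study "will receive appropriate therapies according to local ANC guidelines for treatment of these diseases in pregnancy". No drug is named and AZ is not carved out for the SP arm. Women with *T. pallidum* "will receive standard dosing regimen of benzathine penicillin G consistent with local ANC guidelines". The section closes: "Please refer to Section 5.5 (Concomitant Medications) and/or drug inserts for further information regarding potential interactions between study drugs and other treatment agents".
- **Section 6.1.8 (Unscheduled Visit):** permits additional treatments that local or national antenatal guidelines recommend.
- **Section 1.3.2.3 (background):** "Single oral doses of 1000 mg and 2000 mg of azithromycin are recommended for chlamydial and gonococcal infections".
- **Section 1.6 (rationale, item 5):** treating and preventing STIs is said to lower adverse pregnancy outcomes by about 30%, so AZ's activity is expected to add benefit.
- **Section 9.2:** the primary analysis set is ITT. The secondary per-protocol set will "exclude subjects who withdraw from study drug and switch to standard of care IPTp treatment". It does not mention AZ taken for an STI in the SP arm. Sensitivity analyses are to be defined for both sets.

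**The concern.** Both instructions are mandatory and can apply to the same woman. If her local guideline calls for AZ, the investigator must breach either 5.5 or 5.7, and the protocol does not say which. The protocol itself makes the situation foreseeable, because it calls AZ recommended for two of the three infections covered by 5.7.

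Two things are at stake. The first is consistency of care and of the control condition: with no precedence rule, sites may choose differently in an open-label trial. The second is the treatment contrast. SP women given AZ would receive one component of the test product, in the subgroup where its STI activity is expected to matter. That would narrow the difference on the primary composite. It would also narrow it on the STI endpoints that rest on laboratory results at Weeks 36-38: the laboratory part of key secondary endpoint 6 and other secondary endpoints 10 to 12.

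**Working it through.** **Step 1. Where the rules collide.**

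| Situation in the SP arm | Section 5.5 | Section 5.7 | Conflict? |
|---|---|---|---|
| *T. pallidum* | AZ and CQ barred | benzathine penicillin G | No |
| Symptomatic *C. trachomatis* or *N. gonorrhoeae*, local guideline does not call for AZ | AZ barred | local guideline | No |
| Symptomatic *C. trachomatis* or *N. gonorrhoeae*, local guideline calls for AZ | AZ barred | local guideline, i.e. AZ | Yes, with no precedence stated |

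For *T. vaginalis* the same logic applies, but the statement in 1.3.2.3 does not cover it. In the AZCQ arm there is no contradiction, because 5.5 allows medication consistent with the AZ and CQ package inserts.

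**Step 2. Does the cross-reference resolve it?** No. Section 5.7 sends the reader to 5.5 for interactions between study drugs and other agents. It does not make the choice of STI treatment subject to the bar in 5.5.

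**Step 3. Does the sample size allow for it?** Inputs: one-sided alpha 0.000625, about 90% power, RR 0.80, 1:1 allocation, looks at 50/70/100%, gamma(-4) alpha spending and gamma(-6) beta spending (Sections 5, 9.1 and 9.5). The fixed-sample total on the log risk ratio scale is

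N = 2 × (z₁₋α + z₀.₉₀)² × [(1−p₁)/p₁ + (1−p₂)/p₂] / (ln 0.80)².

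For SP rate p₁ = 0.28 and p₂ = 0.80 × 0.28 = 0.224 this gives 4930. The group-sequential inflation, found by numerical integration, is 1.0228, and 4930 × 1.0228 ≈ 5042. All columns of Table 4, using 0.44 from Table 5 for the open-ended last one:

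| SP rate | 0.28 | 0.32 | 0.36 | 0.40 | 0.44 |
|---|---|---|---|---|---|
| Table 4 | 5044 | 4206 | 3552 | 3030 | 2602 |
| Recomputed | 5042 | 4204 | 3551 | 3027 | 2602 |

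Table 4 is reproduced from RR 0.80 alone. It contains no allowance for AZ use in the SP arm.

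**Step 4. Illustration only.** Two quantities are needed that the documents do not give: the share c of SP women who receive AZ, and the fraction s of the assumed 20% risk reduction that they gain from it. Both are assumptions here. The SP rate becomes p₁(1 − 0.20·s·c), so the observed RR is 0.80/(1 − 0.20·s·c). For SP 0.28 and N = 5044, with group-sequential efficacy bounds and futility ignored:

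| c | RR (s = 0.5 to 1) | Power (s = 0.5 to 1) |
|---|---|---|
| 0 | 0.800 | 90.2% |
| 5% | 0.804 to 0.808 | 88.2% to 85.9% |
| 10% | 0.808 to 0.816 | 85.9% to 80.4% |
| 20.8% | 0.817 to 0.835 | 79.9% to 64.8% |

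Results for SP 0.36 and N = 3552 agree within 0.1 point. The table shows direction and sensitivity. It is not a forecast.

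**The case against.** The strongest reply is that 5.5 is specific and absolute while 5.7 is general, so a site can satisfy both by using another guideline-listed drug. The protocol mentions other agents in this setting: cefixime in the presumptive-treatment trial (1.3.2.3), and erythromycin as a comparator for *C. trachomatis* in pregnancy (1.3.2.4.1). The local guidelines are not in the documents, and the recommendation in 1.3.2.3 cites international guides. This stands as a limit: the conflict is conditional. It does not supply the missing precedence rule.

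Several stronger readings are tempting but not supported:

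- *The SP arm may receive half of the test combination, uncontrolled.* Section 5.5 prohibits AZ and all medication is recorded. One STI dose of 1000 or 2000 mg is also far from the test regimen: "A total AZ dose of 3000 mg to be used for each IPTp treatment course", given three times.
- *Some 5% to 28% of SP women are affected.* Section 1.3.2.3 gives symptomatic prevalence of 5.3-20.8% for *C. trachomatis* and 1.7-7% for *N. gonorrhoeae*. Complete overlap at the low end (5.3%) and none at the high end (20.8 + 7 = 27.8%) yields that range. These are antenatal-clinic prevalences, not incidence after randomization. Exclusion 15 arguably removes women who already need an interfering drug at entry.
- *Power falls to 65%.* That needs 20.8% exposure and the full AZCQ effect from STI-dose AZ. Nothing supports that. Section 1.3.2.2 reports only 33% Day 28 efficacy for AZ alone in treating malaria, at 1000 mg daily for three days.
- *The STI endpoint is lost.* Key secondary endpoint 6 also counts episodes by clinical presentation, so a woman treated for a symptomatic STI is already counted. Any effective antibiotic could clear the infection before Weeks 36-38, so part of the dilution would occur under either rule.
- *SP women given AZ should leave the per-protocol set.* They would mostly be women with STIs, who are at higher risk of poor outcome. Removing them from one arm only would select on a post-randomization event and favour SP. Nor are they parallel to AZCQ women who abandon their assigned regimen.

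It is also fair that detailed handling of such use may sit in the SAP, which was not available. Its absence from the protocol is not counted as an error.

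**Conclusion.** The point holds as an unresolved, conditional contradiction. Where a local guideline uses AZ for chlamydial or gonococcal infection, 5.5 and 5.7 direct opposite actions for an SP-arm woman and the protocol gives no precedence. Syphilis is outside it.

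Any resulting bias runs toward no difference on the primary and STI comparisons. It threatens power and consistent care. A reader should not infer a risk of a false superiority claim. Its size cannot be estimated, because the documents give neither the local guidelines nor the expected AZ use after randomization nor the effect of a single STI dose on pregnancy outcome. The only firm quantitative statement is that Table 4, reproduced within 3 subjects in every column, makes no allowance for it. The conclusion rests on the wording of the two sections and on the assumption that at least one participating site's guideline includes AZ.

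**What to change.** Reconcile Sections 5.5 and 5.7 into one rule for women who need STI treatment, chosen by the sponsor's clinicians and applied at all sites. Check Section 6.1.8 against it. This review does not say which rule is right.

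From the concomitant-medication data already collected, report the number of women per arm with non-study AZ or CQ use. Examine the influence of that use in a sensitivity analysis that treats both arms alike, specified in Section 9.2 or the SAP. Do not add a one-sided per-protocol exclusion.

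The cost is a wording change and one small additional analysis. No new data are needed, and the sample size and primary analysis are unchanged.
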